### Design

Twelve pairs of matched schools will be randomly selected: half will receive a salad bar (Intervention; replacing all other FVs) and half will only serve pre-portioned FVs, standard under the NSLP (Control). Thus, groups will have different FV presentation methods; however all schools will be operating under a policy requiring students to take at least one FV serving [44]. In contrast to prior salad bar research, [28] salad bars in the current study will replace all other FVs on the lunch line, and students can select their entire meal from the salad bar. This implementation model facilitates a more rigorous comparison between schools with and without salad bars than that conducted in prior research. Schools will be matched on Title I status (a proxy for socioeconomic status [SES]) and percent of racial/ethnic minority students based on higher obesity risk. Dietary intake at lunch will be objectively assessed in each pair of schools, prior to (baseline), and 4–6 weeks after salad bars are installed (post), resulting in ~ 14,160 lunch observations throughout the study duration. The primary dependent variable of interest is change in FV intake, assessed using digital imagery plate waste methods. Cafeteria sales and NSLP participation data will also be examined to assess the potential impact of salad bars on these critical revenue sources. Finally, we will assess implementation practices and cafeteria personnel’s perspectives, to identify barriers and facilitators to salad bars and inform sustainability efforts.

Prior to random selection, each school will be assigned to one of 4 categories based on sociodemographic variables. We used information from schools that received salad bars in the first 2 years of the district’s program (prior to the current study) to develop matching procedures. Matching was based on: 1) Title I status, which includes % free and reduced-price lunch, and 2) % of students from racial/ethnic backgrounds at higher risk of obesity (Native American, African American/Black, Latinx, Native Hawaiian/Pacific Islander, more than one race). Four categories of schools resulted: A = < 40% minoritized AND not Title I; B = 40–60% minoritized AND not Title I; C = 40–60% minoritized AND Title I; and D = > 60% minoritized AND Title I. Matching procedures were then applied to the remaining 91 schools, demonstrating that each category has adequate numbers of schools in each year of this study to successfully execute the proposed aims.

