As illustrated in Fig. 1 and 16 different schools will be included (A1➔D4), 4 from each sociodemographic category. In Year 1, 8 schools will be randomly selected: 4 with salad bars (A1➔D1; Intervention), matched with 4 serving pre-portioned FVs only (A2➔D2; Control). In Year 2, these 4 control schools will receive salad bars and become Intervention schools, and will be matched with 4 new, randomly selected Control schools (A3➔D3). These procedures will be repeated in Year 3, with A3➔D3 becoming Intervention schools, matched with new randomly selected Control schools (A4➔D4). There will ultimately be 12 pairs of matched schools (12 Intervention [shaded green in Fig. 1] and 12 Control [shaded yellow]).

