Analyses are dictated by the cluster RCT study design. Data are hierarchical, gathered in multiple levels. The first level of measurement is from students, clustered within schools, the second level of measurement. We are measuring consumption based on students, yet their treatment assignment is defined by the school’s assignment. This nested structure must be considered in analyses as the assignment of intervention to the schools can result in students within schools being positively correlated for the outcomes. Without accounting for correlated nature of the data, Type 1 error rate for the intervention effect might be inflated and the significance of the study findings misinterpreted. Multilevel Linear Modeling (MLM) is a type of regression used to analyze nested data as it can accommodate fixed and random effects and correlated observations within units of assignment (schools). SAS PROC MIXED (for continuous variables) and PROC GLIMMIX (for dichotomous and polytomous data) have MLM applications which take into account random effects and correlated observations and will be used in these analyses. Potential covariates include grade, NSLP participation, and month of assessment, and factors related to the school cafeteria environment that might differ between schools (e.g., lunch duration), where appropriate. Using these models, we will evaluate differences between Intervention and Controls schools in types and variety of FVs and categories of vegetables selected, and subsequent consumption (% consumed/wasted) at baseline and 4–6 weeks after salad bars are installed. Variety will be recorded as the number of different types of FVs selected for each meal, and the number of categories of vegetables (ranging from 1 to 5; corresponding with USDA categorization) [44]. For the primary outcome (FV consumption), plate waste ratings will be calculated for fruits, vegetables, each specific FV category, and also averaged across FVs. We will also evaluate the effect of location of FVs (salad bar, lunch line, or at the point of sale) and serving type (self-serve, pre-portioned) of each item on FV selection and consumption to inform best implementation practices.

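### The stated model nests students in schools only, so a test of change in FV intake could take its error from individual lunches instead of school rating occasions

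*Protocol article*

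**What the plan says.** The Design section of the protocol article states: "The primary dependent variable of interest is change in FV intake, assessed using digital imagery plate waste methods". The Analyses section then sets the hierarchy: "The first level of measurement is from students, clustered within schools, the second level of measurement". It presents multilevel modelling in SAS as the way to handle correlation within the school, and gives protection against an inflated Type 1 error rate as the reason. It names no level for the rating occasion.

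The comparison itself is worded as follows: "Using these models, we will evaluate differences between Intervention and Controls schools in types and variety of FVs and categories of vegetables selected", together with consumption, at baseline and 4–6 weeks after installation. No arm-by-time term is written out.

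Matching enters an analysis only through the paired t-tests on sales and NSLP participation. The sociodemographic categories A to D enter the models as main effects, but they are the matching strata, not the pairs. Design also has schools move between arms from one year to the next: "these 4 control schools will receive salad bars and become Intervention schools".

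**The concern.** Under Cafeteria procedures, tray labels serve to match the two photographs of one lunch. No identifier linking a child from baseline to post is described. Change in intake is therefore a difference between two school-occasion means, and its natural error is how much those means move for reasons specific to the school and the day.

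A random intercept for school captures only what is stable about the school. That part drops out of a baseline-to-post contrast. What remains as error in a two-level model is lunch-to-lunch variation divided by about 295. A school-specific day effect is shared by every lunch rated that day, so even a small one can exceed this error. The primary p-value and confidence interval would then be too optimistic, in a trial whose unit of assignment is the school.

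**Working it through.** **1. The plan's own figure.** Inputs from Power analysis: J = 16 schools, n = 295 lunches, two-sided α = 0.05, power 80%, ICC ρ = 0.01, 0.05, 0.10. Minimum detectable effect = λ·√(4[ρ + (1−ρ)/n]/J), with λ from the noncentral t on J − 2 = 14 df. Results are 0.174, 0.348 and 0.484, against the stated 0.17, 0.35 and 0.48. The figures reproduce. The calculation uses school-level error for a comparison without a time dimension, and does not split the ICC into stable and time-specific parts.

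**2. Rating days.** Target population and sample expects about 295 lunches per school on each assessment date. With 12 pairs, 295 × 24 = 7,080 per time point, and 7,080 × 2 = 14,160. Both totals match the article, so the counts imply one rating day per school per time point.

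**3. Error of the change contrast.** Set total variance to 1. Let CAC be the cluster autocorrelation, the share of between-school variance that is stable from baseline to post. CAC is an assumption, since the article gives no value. The school-by-time share is s = ρ(1 − CAC).

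- True variance per school-occasion, once the stable part has cancelled: s + (1 − ρ)/n
- Variance used by a model with a school intercept only: (s + 1 − ρ)/n
- Ratio R = (ns + 1 − ρ)/(s + 1 − ρ)
- Type I error = 2[1 − Φ(1.96/√R)]

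Example, ρ = 0.05 and CAC = 0.8: s = 0.01; R = (2.95 + 0.95)/(0.01 + 0.95) = 4.06; √R = 2.02; type I error 33%.

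| ICC | CAC 1.0 | CAC 0.9 | CAC 0.8 | CAC 0.5 |
|---|---|---|---|---|
| 0.01 | 5% | 8.5% | 12% | 21% |
| 0.05 | 5% | 22% | 33% | 50% |
| 0.10 | 5% | 34% | 47% | 63% |

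**4. Simulation.** The planned layout (16 schools, 12 pairs, two occasions) was simulated under no effect and fitted by REML, with 400 replicates per setting. With a school intercept only, rejection was 10.5% (ICC 0.01, CAC 0.8), 24% (0.05, 0.9), 35% (0.05, 0.8), 48% (0.10, 0.8) and 5% (0.05, 1.0). Monte Carlo standard error is about 1 point near 5% and 2.4 points near 35%.

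**5. Variance shared within pairs.** At ICC 0.05 and CAC 0.8, if half of the school-by-time variance is common to both schools of a pair, the rate falls from 35% to 20%. If all of it is shared, the rate is 5%.

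**6. Candidate remedies.** Across the five settings in step 4, a random school-occasion term (t, 22 df) gave 3–6%. A one-sample t-test on pair-level differences-in-change (11 df) gave about 4–6%. In the two settings of step 5, the school-occasion model without a pair term was conservative (1.5% and 0.25%), while the pair-level test gave 3.5% and 4%.

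**7. The other reading.** A two-sample t-test of the 12 against 12 post means rejected in at most 1% of runs. It is conservative because 8 schools appear in both arms. It does not test change.

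**The case against.** The strongest reply is that the article never writes out the random-effects specification. A full analysis plan, not shown here, could add a school-occasion term, and an article may fairly leave that detail to it. This stands against any claim that the final model will certainly lack the term. It does not remove the point, because the article does more than stay silent: it fixes two levels, names the school as the unit within which observations correlate, and offers that structure as its protection against Type 1 error. For a change outcome, that structure does not protect.

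Second, pairs are rated concurrently, on the same menu cycle where possible, and month is controlled (Design). These measures remove effects common to both schools, and step 5 shows how much that can help. They do not remove effects particular to one school on one day.

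Three stronger inferences are tempting, and the documents do not support them:

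- **A false-positive rate of 20–50% as a property of the plan.** That range needs a school-by-time share of about 0.5% to 2.5% of total variance, which is not given and is not the same quantity as the plan's ICC.
- **The missing pair term as a cause of false positives.** Effects shared within a pair cancel from the contrast, so leaving the pair out tends to be conservative.
- **Adjustment for an outcome.** The list reads "Potential covariates include grade, NSLP participation, and month of assessment", and participation is also an outcome. But Cafeteria environment has participation rates obtained before baseline, and nothing says that a post-installation value enters the intake models. Only a clarification is needed.

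**Conclusion.** The point holds conditionally. As described, the two-level structure does not supply the right error term for the primary variable. If the arm-by-time contrast is fitted with a school intercept only, type I error is about 8.5–47% across the plan's ICCs with CAC between 0.8 and 0.9. The assumptions are one rating day per school per time point, 295 lunches per occasion, no linkage of children, and school-by-time effects that are independent between schools. The rate is 5% with no school-by-time variance, lower than these figures if part of that variance is shared within pairs, and above 60% at ICC 0.10 with CAC 0.5.

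If the Analyses wording means separate comparisons at baseline and at post, this inflation does not arise, but the stated primary variable goes untested. Either reading calls for a correction.

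The Discussion reports that one pair lost its post-ratings and argues from lunch numbers that power will be adequate even if collection does not resume. Years 1 and 2 provide 4 + 4 = 8 pairs, so at most 7 would be complete. An analysis with lunches as the error unit would hide that loss.

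**What to change.** State the primary test as the arm-by-time (baseline/post) contrast on FV intake. Then do one of the following:

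- Fit the multilevel model with a random effect for school and a random effect for school × year × time (the school occasion), using Kenward-Roger degrees of freedom. Adding the pair-by-time block matches the design and may add precision.
- Compute one difference-in-change per matched pair and use a one-sample t-test: 11 df with 12 pairs, or at most 6 df with 7 complete pairs if Year 3 is not collected.

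State also that NSLP participation, if used as a covariate in the intake models, enters at the pre-baseline value already being collected.

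The cost is a change of wording and a few lines of SAS code, with no new data. Standard errors will be wider, and precision will depend on the number of schools and pairs more than on the number of lunches.

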In sum, there is an urgent need to improve the quality of children’s dietary intake. Optimizing school meals within the NSLP can have a significant public health impact. Tremendous resources have been invested in school salad bars as a means to increase FV intake, yet it is not known if they achieve this goal. By randomly selecting schools receiving salad bars, matching them with those serving pre-portioned FV only, and conducting a comprehensive, longitudinal evaluation that includes objective, validated assessments of dietary intake, this investigation will address these critical gaps. Specifically, this study will identify: (1) how salad bars impact dietary consumption in NSLP lunches, and (2) consequences of, and barriers and facilitators associated with, salad bar implementation. It will also examine the potential moderating role of the school-level sociodemographic factors of percent high obesity risk racial/ethnic minority students and Title I status on dietary consumption, and salad bar implementation barriers and facilitators. In the current study, all FVs on the salad bars will be fresh and *replace* all fixed portion FVs on the serving line. All schools will operate under a policy requiring students to take at least one FV serving [44]. This will allow examination of the independent and combined impact of variety and choice, two mechanisms with potential to increase FV intake, within the NSLP. We hypothesize that schools with salad bars will manifest greater increases in both FV selection and consumption, and decreases in FV waste, compared with schools without salad bars. In addition, we hypothesize that schools with salad bars will have greater improvements in dietary quality and reductions in total energy intake at lunch, compared with schools without salad bars.

Data from this trial will yield some of the clearest evidence related to salad bars to date, providing a strong evidence base to evaluate school nutrition policies designed to enhance dietary intake and reduce health disparities within the NSLP. Results can guide resource allocation and inform targeted interventions and policies designed to reduce obesity.

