**Fig. 1 Fig1:**
[figure not shown]
Design of wait-list control randomized controlled trial of school salad bars

Each pair of Intervention and Control schools will be assessed concurrently, minimizing the threats maturation and history effects pose to internal validity [45]. Baseline and post-assessments within each pair will be conducted on days with the same menu cycle whenever possible, which controls for potential confounds, such as the varying palatability of meals and seasonal variations in food availability (the district’s schools have 5 week menu cycles). We will also control for month of assessment in all analyses. This is particularly important in the elementary school setting, where students are continually adjusting to the environment and school breaks can affect eating habits [46]. Inclusion of baseline assessments will allow us to control for any baseline differences between schools. Raters will be masked to avoid potential bias. Moreover, conducting independent double ratings of ~ 20% of meals will further minimize the influence of any potential bias. Finally, this study’s internal validity is enhanced by matching schools on key variables prior to randomization, so that they differ primarily on presence of a salad bar [45]. Matching procedures were carefully developed to evaluate how school-level factors of race/ethnicity and SES might moderate the impact of salad bars. Other variables that could potentially vary between schools and impact outcomes will be carefully monitored and considered in analyses (e.g., NSLP participation or school environment factors). Plate waste assessments will be conducted in wait list control schools during two consecutive years; however, students will not know the purpose of the assessments, and their prior experience with these (minimally obtrusive) methods is not likely to alter dietary behaviors during the following school year.

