We will evaluate differences in dietary quality (assessed with the HEI) [57] for the total lunch and energy intake (kcals) for the total lunch, FVs, non-FVs, and beverages between Intervention and Control schools. MLM will be applied to examine the association between levels of FV intake and overall calorie consumption at lunch, both independent of school group as well as between Intervention and Control schools, to inform obesity prevention efforts.

Monthly sales (and reimbursements) and NSLP participation data will be characterized using descriptive statistics and graphical approaches. Changes in FV sales (and reimbursements) per student (based on enrollment) and % NSLP participation will be calculated (based on the total number of days lunch was served), evaluated by month. Schools will be compared on these outcomes using paired t-tests (matching on month for each school pair). Responses from cafeteria surveys and process logs will be examined to identify barriers and facilitators and implementation differences related to salad bars to inform sustainability. These variables will also be considered as potential factors explaining any differential findings between schools. Open-ended survey responses will be qualitatively examined for common themes by two independent raters, guided by thematic analysis, to identify, analyze and report themes within and across data [68]. This realistic method allows for meaning to come from participants, rather than from pre-existing codes [69].

To examine the potential differential responses to salad bars among sociodemographic groups, main effects for Title I status and race/ethnicity school group (A through D) will be examined in Aims 1 through 3 analyses. If main effects are observed, models will be stratified by sociodemographic group and moderator analyses considered as appropriate.

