Since the initiation of this study, we have completed collection of Year 1 and the majority of Year 2 data, yielding > 14,000 images of school lunches. Data collection was paused in March 2020 when schools closed due to COVID-19, canceling post-ratings of one pair of schools scheduled to be rated that month. Students returned to school in Fall 2020, yet salad bars have not yet re-opened. The COVID-19 pandemic highlighted the critical role of school meals in addressing food security, and simultaneously placed enormous pressure on school nutrition programs to ensure students were fed [71]. When school buildings were closed in the Spring and Summer of 2020, schools set up meal distribution sites and delivery systems (all while understaffed and under-resourced). The return to school in 2020-21 brought new challenges related to increased demands for school meals, risk mitigation, staffing shortages, and supply chain disruptions. In response, the USDA issued national meal pattern waivers, allowing schools to veer from NSLP nutritional standards—including those related to milk, whole grains and sodium set forth by the HHKFA—and mandated universal free meals [71–73]. Many districts, including the one in this investigation, transitioned to more pre-packaged meals during this time and temporarily eliminated a la carte offerings. Although these temporary waivers helped schools meet the meal demands during that time, there is concern that diet quality has been compromised [71–73]. This is a particular concern given extension of nutrition waivers and the enhanced role of schools in addressing food security [71–73]. There is thus a great need to investigate how these changes have impacted children’s nutrition.

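### The Analyses section tests differences between arms, not the difference in change the trial asks about; as a school-clustered level comparison it would take in year-to-year drift, because 8 of 16 schools switch arm

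*Protocol article*

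**What the plan says.** **The question.** Background predicts that "schools with salad bars will manifest greater increases in both FV selection and consumption", with matching predictions for dietary quality and energy. Design names change in FV intake as the primary dependent variable.

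**The tests.** Analyses says "we will evaluate differences between Intervention and Controls schools in types and variety of FVs and categories of vegetables selected", then adds consumption, with both baseline and the 4–6 week visit in view. For the next outcomes it says "We will evaluate differences in dietary quality" and energy between the two groups of schools, without mentioning time. The models are multilevel, with students within schools. On adjustment: "Potential covariates include grade, NSLP participation, and month of assessment", plus cafeteria factors. Neither study year nor matched pair is named, and no arm-by-time term or change score is written for these outcomes.

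**The layout.** "In Year 2, these 4 control schools will receive salad bars and become Intervention schools"; the same happens to the next set in Year 3. So A2–D2 and A3–D3, 8 of 16 schools, each serve once as Control and then, a year later, as Intervention.

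**The protection claimed.** The text after Fig. 1 says "Each pair of Intervention and Control schools will be assessed concurrently, minimizing the threats maturation and history effects pose to internal validity". It also says that baseline data will allow control of baseline differences and that month will be controlled in all analyses.

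**The concern.** A difference between arms and a difference in change between arms are not interchangeable in this design. All switching goes one way, Control first and Intervention a year later. A model with one random intercept per school treats a switching school as its own control, and with about 295 lunches per visit that comparison is very precise. It therefore dominates the estimate, and the concurrent matched comparison that Design relies on gets little weight. Each within-school contrast equals the salad-bar effect plus whatever changed between the two years. Without a year term the model cannot separate the two, so drift in menus, policy or appetite could look like a salad-bar effect or hide one. This is bias in the estimate, separate from any error in its standard error. It would reach FV selection, FV consumption, diet quality and energy.

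**Working it through.** **1. The plan's own figures.** Power analysis gives 16 schools, 295 lunches per school, ICC 0.01 / 0.05 / 0.10, two-sided α 0.05 and 80% power. Minimum detectable effect = (t[0.975, 14 df] + t[0.80, 14 df]) × √(4 × (ICC + (1 − ICC)/295)/16). At ICC 0.05: (2.145 + 0.868) × √(0.05322/4) = 3.013 × 0.11535 = 0.348. The three results are 0.174 / 0.348 / 0.484, against 0.17 / 0.35 / 0.48 stated. Lunch counts also agree: 24 × 295 = 7,080, and twice that is 14,160.

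**2. Layout from Design, per sociodemographic category.** School 1 is Intervention in Year 1 only. School 2 is Control in Year 1 and Intervention in Year 2. School 3 is Control in Year 2 and Intervention in Year 3. School 4 is Control in Year 3 only. Four categories give 16 schools, 24 school-years and 8 switching schools.

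**3. Level comparison at follow-up, random school intercept, no year term.** Let s = (1 − ICC)/295 (total SD = 1) and let d be a common linear drift in SD per year. Two sources feed the arm effect:

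- Within the 8 switching schools: variance 2s/8 = s/4, expectation effect + d.
- Between the four Year 1 Intervention-only schools and the four Year 3 Control-only schools: variance (ICC + s)/2, expectation effect − 2d.

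Inverse-variance weighting gives the within-school weight w = 2(ICC + s) / [2(ICC + s) + s]. The share of drift entering the arm effect is w − 2(1 − w) = 3w − 2, and SE = √(w·s/4).

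| ICC | s | w | Share of d | SE |
|---|---|---|---|---|
| 0.01 | 0.00336 | 0.8884 | 0.67 | 0.027 |
| 0.05 | 0.00322 | 0.9706 | 0.91 | 0.028 |
| 0.10 | 0.00305 | 0.9854 | 0.96 | 0.027 |

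With Years 1–2 only, four schools switch, w = (ICC + s)/(ICC + 2s) = 0.799 / 0.943 / 0.971, and the share is 2w − 1 = 0.60 / 0.89 / 0.94. If baseline and follow-up are pooled over three years, s is halved and 3w − 2 becomes 0.80 / 0.95 / 0.98.

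**4. False rejection with no true effect.** P(|Z + share × d/SE| > 1.96). Example at ICC 0.05, d = 0.10: 0.0912/0.028 = 3.26, giving 90%. The drifts are assumptions.

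| d (SD/year) | Three years, ICC 0.01 / 0.05 / 0.10 | Two years |
|---|---|---|
| 0.02 | 8 / 10 / 11% | 6 / 7 / 8% |
| 0.05 | 23 / 37 / 41% | 13 / 21 / 23% |
| 0.10 | 68 / 90 / 94% | 37 / 62 / 69% |

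Simulation with the school variance estimated (600 runs per cell) agrees in pattern. At ICC 0.05 over three years the level model rejects 6% with no drift, 35% at 0.05 and 92% at 0.10.

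**5. Alternatives, same simulation, three years, drift 0 to 0.20.**

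- Level model plus study year: drift share exactly 0, rejection about 5–9%. SE becomes 0.033 / 0.055 / 0.074.
- Arm-by-time without a year term: about 4–6% at every drift. The baseline arm difference carries the same drift, so subtraction removes it.
- Paired test on within-pair differences in change: about 4–6%.
- Follow-up adjusted for the school-year baseline mean: 9–17%, not rising materially with drift.

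**6. School-by-year variation, no drift, ICC 0.05.** If school-year variance is assumed to be 20% of the school variance, the level model with a school effect only rejects 32%. With visit-level noise of 10% added, arm-by-time rejects 22%, while the paired change test stays at 5–7%.

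**The case against.** The strongest reply is that a condensed article is being read as a fixed model. Design makes change the primary variable and says baseline will be controlled, and the quoted sentence in Analyses goes on to include both visits. No equation and no follow-up-only test is written. A change analysis cancels common drift even without a year term. Nor does the article say how a school that serves in both arms is coded. If each school-year is its own cluster, every year has 4 Intervention and 4 Control schools and common drift cancels, though that coding has a dependence problem of its own. The coding of month is not stated either: dated months would carry the year. Process logs adds that policy changes will be monitored for consideration in analyses.

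Most of this stands, and it rules out saying that the planned test is biased. It does not remove the point. Design's statements show intent without a model form, and Analyses states a different comparison. This is not only compression, because the same section specifies change and paired tests matched by school pair for the sales and participation data, but not for the primary outcome. Power analysis counts 8 Intervention and 8 Control independent schools, so the statistical text does not acknowledge the switching. The reasons given for adjusting for month are seasonal ones, and Analyses lists month only as a potential covariate.

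A reader might also infer that the pandemic has already contaminated the comparison, since Discussion says "Many districts, including the one in this investigation, transitioned to more pre-packaged meals during this time". The documents do not support that. Collection stopped in March 2020 with Year 1 and most of Year 2 complete, so existing data predate the change. It would matter only if Year 3 is collected afterwards, and whether collection resumes is left open.

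**Conclusion.** The concern holds in part. The mismatch is in the text: the question is about change, while the stated tests for intake, diet quality and energy are arm differences in school-clustered models with no year or pair term. If those words are followed with one random intercept per school and no year information, 67–96% of a common linear drift enters the arm effect over three years, and 60–94% over two.

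The further step, that the trial will reject for drift, is not established. It needs a level reading, an intercept carried across years, month not coded by date, and a real drift. The article commits to none of the first three and gives no figure for the fourth. At 0.02 SD per year the excess is modest (8–11% against 5%); at 0.10 it is severe (68–94%). All rates are at nominal 5%, before the planned multiplicity correction. One reading of the primary test is safe against common drift and another is not, so the choice should be written down before the arms are compared.

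**What to change.** In Analyses:

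- For each intake, diet-quality and energy outcome, name one test: the arm-by-time contrast with both main effects kept, or the within-pair difference in change.
- Include the matched pair-by-year set (or study year) as a fixed effect, and a school-year random effect alongside school.
- A school-year intercept shared by both visits cancels out of a change. An arm-by-time model therefore also needs a random effect for each school visit to cover the visit-level noise in step 6; the within-pair form handles that noise directly.
- State that month is month of the year, so that calendar time is carried by the year or pair term.
- Draw no conclusion from a follow-up-only or pooled arm term fitted without year.

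The cost is in the analysis only; no new data are needed. Study year takes 2 degrees of freedom over three years, and twelve pair-by-year sets take 11. Once the change contrast is used, the year term removes no further common drift; its main use is to protect any level comparison that is kept. Such a comparison would show a larger standard error, about 0.055 instead of 0.028 SD at ICC 0.05 with three years.
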